## Abstract

**Background:**

People who are diagnosed with both mental and chronic medical illness present unique challenges for the health care system. In resource-limited settings, such as rural India, people with depression and anxiety are often under-served, due to both stigma and lack of trained providers and resources. These challenges can lead to complications in the management of chronic disease as well as increased suffering for patients, families and communities. In this study, we evaluate the effects of integrating mental health and chronic disease treatment of patients in primary health care (PHC) settings using a collaborative care model to improve the screening, diagnosis and treatment of depression in rural India.

**Methods:**

This study is a multi-level randomized controlled trial among patients with depression or anxiety and co-morbid diabetes, or cardiovascular disease. Aim 1 examines whether patients screened at community health-fairs are more likely to be diagnosed and treated for these co-morbid conditions than patients screened after presenting at PHCs. Aim 2 evaluates the impact of collaborative care compared to usual care in a cluster RCT, randomizing at the level of the PHCs. Intervention arm PHC staff are trained in mental health diagnoses, treatment, and the collaborative care model. The intervention also involves community-based “Healthy Living groups” co-led by Ashas, using cognitive-behavioral strategies to promote healthy behaviors. The primary outcome is severity of common mental disorders, with secondary outcomes being diabetes and cardiovascular risk, staff knowledge and patient perceptions.

**Discussion:**

If effective, our results will contribute to the field in five ways: 1) expand on implementation research in low resource settings by examining how multiple chronic diseases can be treated using integrated low-cost, evidence-based strategies, 2) build the capacity of PHC staff to diagnose and treat mental illness within their existing clinic structure and strengthen referral linkages; 3) link community members to primary care through community-based health fairs and healthy living groups; 4) increase mental health awareness in the community and reduce mental health stigma; 5) demonstrate the potential for intervention scale-up and sustainability.

**Trial registration:**

http://Clinicaltrials.gov: NCT02310932 registered December 8, 2014 URL: https://clinicaltrials.gov/ct2/show/record/NCT02310932; Clinical Trials Registry India: CTRI/2018/04/013001 retrospectively registered on April 4, 2018.

## Background

Chronic, non-communicable diseases have replaced infectious diseases as the number one cause of mortality and disability globally [1–6], and mental disorders are among the leading causes of disability worldwide [7]. In India, the prevalence of common mental disorders (CMD) including depressive and anxiety disorders has been estimated to affect 30-34% of primary care patients [3, 8]. The majority of patients with CMD visiting primary health care centers (PHCs) present with multiple somatic symptoms and are often misdiagnosed, resulting in the receipt of ineffective, symptomatic treatments [9, 10]. In a survey of 12,886 patients visiting a clinic in South India who were participating in a community mental health program it was observed that major depressive disorder and dysthymia accounted for 34% and 22%, respectively, of the total burden of mental illness [11]. Although depression can be effectively treated in PHCs in approximately 60-80% cases, only 10-25% of these cases seek treatment [11], typically due to lack of awareness or perceived stigma and discrimination [11, 12].

Mental disorders increase the risk for both communicable and non-communicable diseases and many of these conditions in turn increase the risk for CMDs [13–15]. Depression, independent of other risk factors in an otherwise healthy person, increases the risk of developing cardiovascular disease (CVD) and adversely impacts cardiac outcomes [16–18]. The depression-CVD co-morbidity not only results in increased mortality but also greater morbidity and disability [19]. Mental disorders and CVD constitute nearly a fifth of the disease burden in India in terms of disability adjusted life years lost [20]. Major coronary risk factors, such as high blood pressure, dyslipidemia, insulin resistance and diabetes are also escalating in this population and correlate positively with the increase in coronary disease [21]. In a study of 103 patients with a recent myocardial infraction attending a cardiology outpatient tertiary care center in Northern India, 25.2% of patients were diagnosed with anxiety or depressive disorder on the Mini International Neuropsychiatric Interview (MINI) [22]. Joseph and Srinivasan [23] reported that 23% of patients who presented with chest pain to a tertiary care facility had diagnosable coronary artery disease (CAD), and the psychological distress in CAD was due to co-morbid psychiatric conditions.

Most chronic non-communicable diseases share modifiable behavioral risk factors, including excessive fat and salt intake, sedentary behaviors, and harmful use of alcohol and tobacco consumption [3, 24], making them excellent candidates for integrated intervention programs [25]. The US-based TEAM care study found that integrating depression and chronic disease care among patients with diabetes mellitus (DM) and/or CAD resulted in greater overall 12-month improvement in glycosylated hemoglobin, LDL cholesterol, systolic blood pressure, depressive symptoms, and quality of life [26, 27]. These interventions not only improve outcomes but are cost-effective too [27, 28]. Both the COPES and SUPRIM trials have found that treatment for depression among patients with CAD was associated with a lower risk of secondary cardiovascular events [29, 30]. The rationale behind integration of the management of CMD with CVD and DM is thus four-fold: 1) both are chronic conditions requiring multiple encounters with the health system and adherence to extended duration treatment regimens; 2) there are considerable cross-benefits of the behavioral intervention strategies; 3) integration of mental health services with those provided for CVD and diabetes are cost effective and could contribute to strengthening health systems by providing shared resources [27, 31, 32]; and 4) barriers to effective treatment are similar, including over-medicalization of diagnosis and management, lack of basic screening and diagnostic tools, insufficient affordable financing mechanisms and lack of trained health-care providers [33].

Many resource-constrained setting, including India, face a shortage of physicians and nurses [34]. India has less than one psychiatrist for every 300,000 population [35], however, in rural areas, which account for 70% of India’s population, this ratio has been estimated at less than one per million [35, 36]. The availability of other mental health professionals such as psychologists, social workers and psychiatric nurses is even less, pointing to the need to train PHC providers and community health workers in identifying and treating these disorders [37–39]. In response, community lay health workers have been successfully trained to improve a range of physical and mental health outcomes. The content of such programs has ranged from cancer education and screening [40] and asthma management [41] to women’s reproductive health [42]. Shifting to lower-level providers and caregivers for on-going patient support shows promise for achieving better outcomes at lower cost [4, 43, 44]. Though India has a long history of use of community health workers in ‘task-shifting’, this has occurred primarily in the fields of maternal and child health and tuberculosis and less so in the field of chronic diseases. A recent study found that non-physician health workers and ‘expert physicians’ agreed on how to correctly apply the World Health Organization (WHO) Cardiovascular Risk Management Package 80% of the time across PHCs in India and Pakistan [45]. In rural Andhra Pradesh, India, non-physician health workers have been found effective in identifying adults with high cardiovascular risk, by following a simple algorithm [43].

The collaborative care model [46–52] involving case managers and consulting psychiatrists in support of primary care providers in the treatment of mental disorders has been successful in providing integrated care for mental health and medical illness in PHC settings [13, 47] and was more effective than standard care (50% vs. 19% reduction in depressive symptoms) in U.S clinics among patients aged 60 and older with major depression and/or dysthymic disorder [47]. A meta-analysis of 37 randomized control trials (RCTs) and 12,355 patients showed that both short term and long term outcomes for depression improved significantly for patients in the collaborative care arm [53]. The integrated collaborative care model has also been found to be cost-effective targeting both depression [54] and chronic medical illness, including diabetes [27, 28, 55]. It has been adapted for primary care with different racial and ethnic groups [56], among patients with different co-morbid conditions, including depression and cancer [57], and depression and DM [58]. The collaborative care model has also demonstrated sustainability in PHC settings [26, 59]. While the collaborative care model has been primarily tested in Western settings, a stepped collaborative care model has been used previously [60] in Indian PHCs to treat mental disorders. Our study extends and adapts the integrated collaborative care model for patients diagnosed with depression and chronic medical conditions in limited resource settings.

The protocol described in this article is an ongoing randomized controlled-trial to implement and evaluate a multi-level community based collaborative care model in rural Ramanagaram district in the state of Karnataka, to improve screening, diagnosis, and treatment of depression in India among patients with co-morbid CMD and either DM or CVD at PHC. The aims of our study are; 1) To examine if community-based screenings for depression, anxiety, DM and CVD risk factors during community health fairs (a) increase subsequent diagnosis of these disorders in PHCs; and/or (b) lead to better linkage and retention in care as compared to the standard PHC based screening. We are using accredited social health activists (ASHAs) to raise awareness and provide outreach for the community health fairs; 2) Implement and evaluate the effects of providing staff training to PHC staff in the collaborative care model of integrated mental health (depression and anxiety) and chronic disease (hypertension, DM, and CVD) as compared to the enhanced standard care model. In addition, we are implementing a community-based risk factor reduction groups (Healthy Living Intervention), co-facilitated by ASHAs, to target risk factors common to both mental illness and chronic physical disease, with group session topics in exercise, diet, adherence to medical regimens, ocial support, coping skills, and problem solving skills; 3) evaluate the effects of the clinic and community-based intervention for co-morbid primary care patients compared to the enhanced standard treatment services.

## Methods

### Study design and overview

As shown in Fig. 1, the study was designed to implement and evaluate the effects of a collaborative care intervention on the screening, diagnosis and treatment of depression among rural Indians with depression or anxiety and either hypertension, diabetes or CVD, who live in villages associated with 50 PHCs in rural Karnataka. The design of randomized controlled trial is described below and compares 1) the enhanced health fair screening condition to standard PHC screening; and 2) community-based and collaborative care to enhanced standard treatment.

**Fig. 1 Fig1:**
[figure not shown]
Study design flowchart

Ethics approval was obtained from the Institutional Ethical Review Board at St. John’s Medical College and Hospital and Committee on Human Research, University of California, San Francisco. All adverse events are identified by trained field staff and assessed by the Principal Investigators. Participants with adverse events are referred to the medical officer at the PHC and or at district hospital for immediate medical intervention as appropriate. Deaths are reported to the St. John’s Institutional Ethics Committee, UCSF IRB, and the Data Safety and Monitoring Board within 5-10 days per protocols approved by the IRBs, the funder and the government of India. Possibly study-related non-serious adverse events are reported to the respective ethics review board by the principal investigators, according to protocol. This study is monitored by a Data Safety and Monitoring Board which consists of a psychiatrist, an expert in community medicine/rural health and a statistician with experience conducting RCTs. The board reviews all procedures biannually related to the protection of study participants, including confidentiality procedures and reports of adverse events. The board has access to data to determine if the trial can continue or needs to be terminated.

### Conceptual framework

We used a multi-level framework based on previous literature on collaborative care to improve screening diagnosis and treatment of depression in primary health settings, and our own extensive work in community medicine and behavior change in India to guide our adaption of the primarily western collaborative care model. Our intervention offers several key innovations for treatment of co-morbid patients by identifying and targeting common risk factors with the help of ASHA and by training PHC staff in the collaborative care model. The “healthy living” intervention described below uses a novel package of evidence-based strategies in a group setting. Our multi-level intervention represents a timely, novel, sustainable and comprehensive approach to co-morbid diagnosis and disease management by integrating multiple existing health care staff and structures into a continuum of care through community based screenings, linkage to and retention in care and ongoing support through the use of community-based groups and mobile technology.

We incorporated constructs from the *Social Ecological Model* [61–66] and *Social Cognitive Theory* [67, 68] because of its emphasis on both interpersonal interactions as well as on specific strategies that promote behavior change; all important to reducing symptoms of depression, anxiety and stress and to increasing health promoting behaviors. In particular, the following three features of this theory guide the delivery of our intervention 1) people and their environments interact continuously, and behaviors are the result of this dynamic bi-directional interaction. Our intervention facilitates this interaction through ASHA at the community level through health fairs, PHC staff at the clinic level, and social support through healthy living groups; 2) By including group-based activities, participants can learn from and motivate each other; 3) The intervention emphasizes skills building, while assisting participants to break down challenges into manageable components necessary to enable sustainable behaviors.

### Setting and randomization

This study is conducted in collaboration with 50 PHCs in rural Ramanagara district of Karnataka state in southern India, each PHC serves a population of 30,000. A typical PHC has a medical officer, pharmacist, staff nurses, female multipurpose health workers (auxiliary nurse-midwives), male multipurpose health workers, ASHA workers, a laboratory technician/assistant, driver and helpers. It includes both outpatient and inpatient areas with four to six beds, as well as space for counseling, minor emergencies, a labor room, a pharmacy and a laboratory. The PHCs were assigned an identification number, and 25 PHCs were randomly assigned by the study statistician using a pseudo-random number generator to the enhanced screening arm linked to community health fairs and the remaining 25 were assigned to the standard screening arm. Subsequently, half of the enhanced screening and standard screening PHCs were randomly assigned to the collaborative care arm and the remaining half was assigned to the standard care treatment condition (Fig. 1). Participants randomized to the intervention group will be stratified by gender. While participants and intervention staff are not blinded, assessment staff are blinded to group assignment.

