### Outcome measures and schedule

The vast majority of the study measures have been used previously in India. Remaining measures (internalized stigma of mental illness, patient satisfaction and clinical vignettes), were adapted and pilot tested during our start-up phase to ensure that they are appropriate for our specific study population and setting. All measures have been translated into Kannada and back translated.

All cohort participants are assessed at baseline, 6 weeks, 3 months, 6 months and 12 months. To minimize attrition, we collect extensive contact information from all participants at enrollment. This includes mobile phone numbers, as well as street addresses, information about landmarks, and the name and phone number of someone who always knows how to reach them. This information is verified and updated during each assessment visit, HLG sessions visit and tracking phone calls and visits. All research materials will be coded with ID numbers only and linked to contact information on a separately stored document kept under lock and key.

To examine if community-based health fair screenings increases subsequent diagnoses in the PHC of patients with co-morbid mental health and chronic disease diagnoses, we use the Kessler-10 [81], MINI [82], and the clinical measures for diabetes and CVD outlined in Table 1. To screen for psychological distress at the initial screening using the Kessler-10, a brief standardized questionnaire that correlates with other commonly used depression screening questionnaires and with the DSM IV diagnoses of both depression and anxiety disorders [81, 83]. At the subsequent confirmatory screening, MINI is used to confirm the diagnosis of anxiety or depressive disorder as per DSM-IV guidelines. We also assess suicidal ideation based on items from the MINI and refer participants at high suicidal risk to the district psychiatrist for further management and treatment.

Linkage and retention in care is measured by the proportion of participants who started treatment and the proportion of these participants who were retained in care throughout the study.

To evaluate the effects of the clinic and community-based intervention for co-morbid primary care patients compared to the enhanced standard treatment services we measure severity of anxiety and depressive symptoms, blood pressure, body mass index and measures for diabetes and cardiac conditions (Table 3).

**Table 3 Tab3:** Outcome measures and study schedule

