#### Screening

To test the hypothesis that, compared to standard screening, enhanced screening will result, on an average, in more people being identified as co-morbid for CMD and CVD/DM during the confirmatory testing at the PHC, we will use a Poisson regression model - or in case of over dispersion, a negative binomial model - with PHC as the unit of analysis, and population size in the catchment area of the PHC included as an offset.

Secondary analysis will explore subsequent linkage and retention in care of enrolled participants first screened at the community health fairs compared to those first screened at PHC. These participants will be compared by examining the proportion of participants who started treatment both by the 6 week follow-up, as well as the proportion retained throughout the study. We will use a mixed-effects logistic regression model with a random intercept for PHC.

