#### Intervention

The primary, intention-to-treat (ITT) analyses will evaluate the impact of the intervention, both in terms of a) return to below-threshold levels for CMD and CVD/DM risk (i.e. dichotomized outcomes), and b) improvement in the levels of the continuous CMD and CVD/DM measures (depression and anxiety scores, BP, HbA1c, LDL, and serum creatinine levels) via logistic and linear mixed-effects regression models respectively, with repeated measures nested within individuals, and individuals nested within PHC, and random intercepts for individuals and PHC [96, 97]. The trajectories of the continuous variables will be examined via the time-by-intervention interaction effect. We will run separate regressions for the various outcomes, to allow us to detect if different variables react to the intervention at different rates. To prevent Type I error inflation, we will lower α accordingly. In all models covariates will be included as necessary.

The sample size of 1250 in each intervention arm (50 participants per PHC), was determined based on achieving 80% power for the ITT analyses regarding the effect of the intervention, and was calculated as follows: we assumed an attrition rate of 20%, and an intra-class correlation (ICC) of 0.1 to account for clustering of participants in PHCs, which reduces the initial sample size to an effective sample size of *n* = 204/group. Pooling data across the three post-intervention measurements triples this number, and subsequent adjustment for repeated measures with an assumed ICC = 0.5, results in a final *effective* sample size of *n* = 306 person-time observations per group. Based on previous research, we assumed 40% of control group participants to recover [98, 99]. With α = .025, the minimum detectable effect size at 80% power is 12% more of the intervention group participants recovering [100]. This is a small effect size according to Cohen [101], and comparable to earlier studies in the US [26]. To test the screening hypothesis, with 25 PHCs per screening condition, 80% power and α = 0.05, the minimum detectable effect in a Poisson regression is 2.1 times as many co-morbid cases identified with the enhanced compared to the standard screening [102]. Although this is a large effect, we deemed it attainable, given the documented under-reporting of mental health in standard care [10, 11], and the intensive nature of our enhanced screening.

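### Care arm was randomised within screening arm, but the intervention models do not name screening arm and leave the choice of covariates open

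*Protocol article*

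**What the plan says.** All references are to the protocol article.

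- **Setting and randomization.** The first step is "25 PHCs were randomly assigned by the study statistician using a pseudo-random number generator to the enhanced screening arm", with the other 25 going to standard screening. In the second step, "half of the enhanced screening and standard screening PHCs were randomly assigned to the collaborative care arm". Treatment is thus allocated within screening arm, in effect a 2×2 layout of 50 PHCs.
- **Statistical analyses, Intervention.** Logistic models (dichotomised outcomes) and linear models (continuous outcomes) are specified "with repeated measures nested within individuals, and individuals nested within PHC, and random intercepts for individuals and PHC". For continuous outcomes, "The trajectories of the continuous variables will be examined via the time-by-intervention interaction effect". On covariates the section says only "In all models covariates will be included as necessary". Screening arm and baseline value are neither named nor excluded.
- **Statistical analyses, opening paragraph.** The two intervention arms are to be compared beforehand to check balance.
- **Statistical analyses, Screening.** The count model is specified "with PHC as the unit of analysis, and population size in the catchment area of the PHC included as an offset". Care arm is not mentioned.
- **Outcome measures and schedule.** "All cohort participants are assessed at baseline, 6 weeks, 3 months, 6 months and 12 months". Table 3 lists PHQ-9 and GAD-7 at baseline.

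**The concern.** A factor that the allocation was stratified on belongs in the analysis. If it is related to outcome and omitted, its variance stays in the between-PHC term although the allocation has already removed it from the treatment contrast. The standard errors are then too large. A relation to outcome is plausible here: enhanced-screening PHCs recruit through village health fairs with door-to-door outreach as well as at the clinic, while standard-screening PHCs recruit clinic attenders only.

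The covariate rule matters as much. A rule with no list, next to a planned balance check, lets covariates be chosen once the data have been seen. In the logistic models this affects more than precision, because a conditional odds ratio depends on which covariates are in the model. The target of the primary estimate is then partly open. The sample size rests on the dichotomised recovery outcome, so this is where a fixed set is most needed.

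**Working it through.** **1. The article's own figures.** Inputs (Intervention section): 1250 per arm, 50 per PHC, 20% attrition, PHC ICC 0.1, three pooled follow-ups with ICC 0.5, 40% control recovery, α = 0.025, 80% power.

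- After attrition: 1250 × 0.8 = 1000 per arm, 40 per PHC.
- Design effect: 1 + 39 × 0.1 = 4.9, so 1000/4.9 = 204.
- Repeated measures: 204.1 × 3/(1 + 2 × 0.5) = 306.
- Detectable difference from 40% at n = 306: 12.4 points two-sided, which rounds to the stated 12. Power at exactly 12 points is 77.1%. One-sided, the detectable difference would be 11.3 points; the article does not state sidedness.

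Both effective sample sizes reproduce. Neither takes credit for adjustment. I take 306 as the article has it.

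**2. Adding screening arm.** Let s be the share of between-PHC variance that screening arm explains. The article gives no figure, so 0% to 20% is an assumption. The variance of a PHC mean falls from 0.1 + 0.9/40 = 0.1225 to 0.1(1 − s) + 0.0225, and effective n rises in inverse proportion.

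| s (assumed) | Variance ratio | Effective n | Power at 12 points | Detectable difference |
|---|---|---|---|---|
| 0% | 1.000 | 306 | 77.1% | 12.4 points |
| 1% | 0.992 | 309 | 77.5% | 12.35 points |
| 5% | 0.959 | 319 | 79.0% | 12.1 points |
| 10% | 0.918 | 333 | 80.9% | 11.9 points |
| 20% | 0.837 | 366 | 84.7% | 11.3 points |

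**3. Cost.** PHC-level degrees of freedom go from 48 to 47. The critical t at two-sided 0.025 goes from 2.3139 to 2.3155, and (2.3155/2.3139)² = 1.0014, equivalent to about 0.14% in variance.

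**4. Bias from omission.** Halving 25 gives cells of 12 and 13. With 25 PHCs per care arm, 13/25 = 0.52 of one arm and 12/25 = 0.48 of the other are enhanced-screening PHCs. Omission shifts the treatment contrast by only 0.52 − 0.48 = 0.04 of whatever difference exists between screening arms.

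**5. Baseline in the continuous models.** Take PHC variance 0.1, person variance 0.4 and residual 0.5 (total 1, within-person correlation 0.5), three follow-ups and 40 people per PHC. Variances per PHC mean are:

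- Follow-up only: 0.1 + 0.4/40 + 0.5/(3 × 40) = 0.114.
- Follow-up mean minus baseline, constant random intercepts as written: 0.5 × (1 + 1/3)/40 = 0.0167, a ratio of 0.146.
- Individual baseline as covariate only: 0.0406, a ratio of 0.356, or about 2.4 times the variance of the change contrast.
- Individual and PHC-mean baseline as covariates: 0.0154, a ratio of 0.135.

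If half of the PHC variance is assumed to vary over time, the ranking reverses: the change contrast has ratio 1.03 and covariate adjustment about 0.64. So whether a baseline covariate helps the continuous models depends on how baseline already enters them, and on a variance pattern that the article does not give.

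**The case against.** The strongest reply is that this is a condensed article, that covariate lists usually sit in an analysis plan that is not shown, and that the covariate sentence leaves room for both screening arm and baseline. This stands in part. A reader might infer that the models leave screening arm out; the text shows only that they do not name it. But the article does more than stay silent. It spells out the model and then states an open rule, and that rule is what needs correcting. That covariates would in fact be chosen after looking at balance is an inference: the wording permits it but does not announce it.

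A second reply is that for continuous outcomes the time-by-intervention term most naturally has baseline among the repeated outcomes. A constant difference between screening arms, or any constant PHC effect, then cancels from the contrast. This also stands. The precision argument for screening arm therefore applies mainly to the dichotomised outcomes, and adding baseline as a covariate to every model could use it twice or lose precision.

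A third reply is that returning below threshold implies starting above it, so the dichotomised baseline says little. That is fair, and it is why the continuous score should be the covariate.

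For the screening count model, care arm is nearly balanced across screening arms and no size of effect can be given. Adding it is optional.

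**Conclusion.** The point holds as one of prespecification: a factor used in the treatment allocation is not named in the analysis, and the covariate rule is open. It is worth correcting, but it does not threaten validity. Bias from omission is small, and standard errors that ignore the stratum err on the cautious side.

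The gain in power at 12 points runs from nil to about 4 percentage points if screening arm explains up to 10% of between-PHC variance, and to about 8 at 20%. These shares are assumptions, and the figures rest on the article's 306 and a two-sided α of 0.025.

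Two stronger readings should be resisted. A reader might posit a standardised difference between screening arms and add the resulting variance to the ICC of 0.1, obtaining a definite loss of sample size. The article gives no such difference, and its ICC for clustering in PHCs would naturally already contain it. A reader might also apply the textbook saving from baseline adjustment at a correlation of 0.5 (1 − 0.5² = 0.75). That formula is for a single follow-up without clustering, which is not this design.

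**What to change.** - Replace the open covariate sentence with a prespecified set, fixed before outcome data are compared by arm.
- Include screening arm as a fixed effect in every intervention model.
- In the models for dichotomised outcomes, include baseline severity as a covariate: PHQ-9 or GAD-7 score, or the corresponding continuous measure for the other outcomes.
- For continuous outcomes, state whether baseline is one of the repeated outcomes or a covariate, and do not use it as both.
- Optionally, add care arm to the screening count model.

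The allocation is known for every PHC, and the baseline measures are already scheduled. The cost is a change of wording and about one PHC-level degree of freedom for screening arm.
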